**Fig. 2 Fig2:**
[figure not shown]
Graphical representation of the shift in distribution in antibiotic-free days (AFD) between baseline and model 3

### Secondary outcome measures

Secondary outcome measures will include antibiotic days and AFD, expressed as continuous variables, at 7, 14 and 28 days; ventilator-free days at 28 days; 28-day mortality and ICU mortality; sequential organ failure assessment (SOFA) score at days 3, 7 and 14; duration of level 2 (high dependency unit) care, level 3 (intensive care unit) care and hospital stay; *Clostridium difficile* and MRSA infections up to hospital discharge, death or 56 days; and antibiotic-resistant pathogen cultures up to hospital discharge, death or 56 days. A healthcare-resource-utilisation analysis will be calculated from the duration of level 2 care, level 3 care and hospital stay up to discharge, death or 56 days.

Since this is a trial of a complex intervention, a process evaluation will be carried out in parallel with this trial. This will evaluate the process of conducting the trial and will aim to determine reasons for potential discrepancies in the expected and observed trial outcome, as well as providing information on the potential implementation of the intervention after trial completion. Additional files outline the detailed study protocol for the process evaluation (see Additional files 1 and 2).

### Data collection

Data are collected on the day of enrolment (day 0); day 3; day 7; day 14; day 28; and date of discharge, death or at 56 days. Clinical data collected include the age, gender, date of admission to the hospital and ICU, reason for admission to the hospital and ICU, functional comorbidities index, acute physiology and chronic health evaluation (APACHE) 2 score at admission, SOFA score, time from MV to suspected VAP, and pathogens cultured from BAL.

Safety measures will be recorded relative to the bronchoscopy and BAL. These will include SaO_2_, heart rate, blood pressure and PaO_2_:FiO_2_. Biological data will include concentrations of IL-1β and IL-8 in the BAL fluid for patients who are randomised to the intervention arm.

### Recruitment process and consent

All patients on the participating ICUs are screened on weekdays for eligibility. Potentially eligible patients are discussed with the ICU consultant to determine the appropriateness of early discontinuation of antibiotics and whether any other safety concerns are present that would exclude the patient.

Consent and assent procedures are in keeping with the legal framework of England, Northern Ireland (Mental Capacity Act, 2005) or Scotland (Adults with Incapacity (Scotland) Act, 2000) for consent/assent of adults without capacity. In England and Northern Ireland informed assent is obtained, where possible, following discussion with the patient’s next of kin (personal consultee). Where a personal consultee is unavailable, assent is provided by a nominated consultee, usually the ICU consultant, providing they are not also a member of the research team. In circumstances where the next of kin are unable to attend the ICU promptly, eliciting their opinion is possible by telephone to inform nominated assent.

In Scotland the patient’s relative or welfare attorney provides the informed consent. If the patient’s relative or welfare attorney is unable to attend the ICU, consent may be provided in a telephone conversation, providing a second member of staff witnesses the discussion.

Patients who recover capacity will be approached to provide retrospective informed consent. The decision as to whether that patient has regained capacity will reside with the treating team. The patient will be given sufficient time to consider the trial information before providing their consent to continued trial involvement.

### Randomisation and blinding

Once consent/assent is obtained, the clinical team informs the laboratory technician who will perform the biomarker test, and the technician then initiates randomisation through the Newcastle Clinical Trials Unit (NCTU). Randomisation is performed using a web-based randomisation service. Patients are randomised to the intervention arm or control arm in a 1:1 ratio by permuted blocks of variable length and stratified by site. The randomisation service generates either an instruction that the patient is randomised to ‘biomarker-guided recommendation on antibiotics: analyse sample on arrival’ or to ‘routine use of antibiotics: do not analyse sample on arrival’. This message is emailed to the technician.

The clinical team is initially blinded to the trial arm since all trial procedures are performed in all participants. Unblinding occurs when the biomarker result is called back to the clinical team after approximately 6 hours. To ensure consistency in unblinding, after this period, the clinical team are also informed if the patient was randomised to the control arm. The technician contacts the clinical team with the results according to local arrangements, which include contacting the on-call ICU consultant, ICU resident or the local principal investigator.

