### Study population

Participants are being recruited from the ICUs of 17 National Health Service (NHS) Trusts in the UK, for a total of 22 ICUs. These ICUs cover a broad case mix of medical, surgical and trauma patients, who are representative of current practice across the NHS.

Patients with suspected VAP who are at least 18 years of age, intubated and mechanically ventilated for 48 hours or more are considered eligible for inclusion in the trial. VAP is suspected based on the presence of a new or worsening chest X-ray or computed tomography (CT) changes consistent with pneumonia in the context of at least two of the following: temperature < 35 °C or > 38 °C; a white cell count of < 4 × 10^9^ / L or > 11 × 10^9^ / L; or purulent tracheal secretions [9]. Patients must also be considered suitable for early discontinuation of antibiotics by the clinical team (i.e. have no extra-pulmonary source of infection that mandates the use of continued antibiotics).

Patients are excluded on the basis of previously published criteria [10] that predict poor tolerance of the bronchoscopy and BAL that have been previously applied in our studies [5, 7]. These are: PaO_2_ < 8kPa on a FiO_2_ > 0.7; positive end-expiratory pressure of > 15 cm H_2_O; peak airway pressure > 35 cm H_2_O; heart rate > 140 beats per minute; mean arterial pressure < 65 mmHg; bleeding diathesis including platelet count < 20 × 10^9^/L or international normalised ratio (INR) > 3; poorly controlled intracranial pressure (>20 mmHg); or ICU consultant deems the procedure not to be safe. Patients may only be randomised to the study once (i.e. they are excluded if they have had previous BAL as part of the study). Patients are also excluded if assent/consent is declined.

Co-enrolment is allowed with observational studies. Co-enrolment with interventional studies is allowed following consideration of any scientific or statistical interactions in accordance with current UK recommendations [11].

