### Statistical analysis

Baseline clinical data will be compared between trial arms for balance using graphical and summary statistics appropriate for the data type of each variable. No formal tests of equality will be carried out. The primary outcome measure will be analysed by a chi-squared test on a 2 × 8 table of study arm versus AFD categories. Secondary outcome measures will be analysed by fitting appropriate generalised linear models with intervention and centre as covariates. Link functions will be determined by the type of outcome variable. A sub-group analysis for patients with trauma or head injury will be included as will a sub-group analysis based on clinician assessment of likelihood of VAP. Data analysis will be performed on an intention-to-treat basis, although other exploratory analyses including per-protocol analysis will be considered. A per-protocol analysis will be performed excluding patients who were randomised to the biomarker-guided recommendation on antibiotics arm, but who had a technical issue with the assay and therefore defaulted to standard care.

A within-trial cost analysis will be undertaken to assess the hospital resource use from the point of randomisation until hospital discharge or death, whichever occurs first, for a maximum of 56 days. Patient-level hospital resource use will be estimated from length of ICU stay and length of hospital stay. Multiple regression analyses will be performed to examine patient factors, which are potentially associated with costs. The robustness of the results will be evaluated using sensitivity analyses.

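### The primary chi-squared test leaves out site, the factor by which randomisation is stratified; the test stays valid but may give up a little power

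*Protocol article*

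**What the plan says.** Under Randomisation and blinding, the protocol article allocates patients 1:1 "by permuted blocks of variable length and stratified by site". Under Statistical analysis it fixes the primary test: "The primary outcome measure will be analysed by a chi-squared test on a 2 × 8 table of study arm versus AFD categories". The next sentence has the secondary outcomes "analysed by fitting appropriate generalised linear models with intervention and centre as covariates". Study population describes recruitment from "17 National Health Service (NHS) Trusts in the UK, for a total of 22 ICUs". The article uses the word site for randomisation and the word centre for analysis, and does not say whether either means the Trust or the ICU.

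**The concern.** When allocation is balanced within sites, differences between sites fall almost equally on both arms. The difference between arms then varies less from trial to trial than a test that ignores site assumes. The usual consequence is a test that is somewhat conservative and less powerful than it could be, by an amount that grows with the variation between sites.

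The plan accepts this reasoning for the secondary outcomes, where centre is in the model, but not for the one confirmatory test. This is not a matter left open for an analysis plan: the article names the test and the table, and a table of arm by AFD category cannot carry site. What is at stake is a few points of power in a trial whose sample size leaves little spare.

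**Working it through.** **Inputs from the article.** Standard care AFD distribution 55/10/10/5/5/5/5/5% and Model 3 distribution 30/20/15/10/10/5/5/5% (Table 1). Effect size 0.0797, 90 per arm, 15% dropout, 210 in total (Primary outcome and sample size). 17 Trusts or 22 ICUs (Study population).

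**Step 1: the plan's own figures.** The effect size is ½ Σ (p1 − p2)²/(p1 + p2). For Model 3:

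½ × (0.0625/0.85 + 0.01/0.30 + 0.0025/0.25 + 0.0025/0.15 + 0.0025/0.15) = ½ × 0.1502 = 0.0751, against 0.075 in Table 1.

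The number per arm is λ/(2 × effect size). Here λ = 14.35 is the noncentrality for 7 degrees of freedom at 5% significance and 80% power. The article states neither level, but both are recovered from Table 1.

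- Model 3: 14.35/0.1502 = 95.5, so 96, as in Table 1.
- Effect size 0.0797: 14.35/0.1594 = 90.03, so 90, as stated.

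The sample size is therefore that of the unstratified 7-df test. With 90 per arm, Model 3 has noncentrality 2 × 90 × 0.0751 = 13.5, a little under 14.35. Its power is thus slightly below 80% before site is considered.

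**Step 2: size of the strata.** 180 analysed patients give 180/22 = 8.2 per ICU or 180/17 = 10.6 per Trust.

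**Step 3: type I error of the planned test.** Trials of 180 patients were simulated with permuted blocks of 2 or 4 within uneven sites and a latent site effect on the AFD categories. With 17 or 22 sites, latent intraclass correlation from 0 to 0.2 and 4,000 replicates per scenario, type I error was 3.6% to 4.7%. A further run with site SD from 0 to 1.0 gave 3.7% to 4.9%. With no site variation at all it was 4.1% (17 sites) and 4.7% (22 sites), so little of the shortfall below 5% can be attributed to site.

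**Step 4: planned test against its stratified version.** The Cochran-Mantel-Haenszel general association test sums, over sites, the observed minus expected counts in each AFD category for one arm. It uses the within-site covariance and refers the result to chi-squared on 7 df. Power under Model 3, planned versus stratified:

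| Assumed site SD (latent log-odds) | Run A, 3,000 replicates | Run B, 2,000 replicates | Run C, whole percentages only |
|---|---|---|---|
| 0 | 77.6 v 75.4 | 80.1 v 77.9 | 77 v 76 |
| 0.4 | not run | 79.9 v 78.9 | 78 v 77 |
| 0.5 | 76.8 v 76.9 | not run | not run |
| 0.8 | 78.5 v 80.7 | 78.2 v 79.9 | 77 v 80 |
| 1.0 | 78.3 v 81.8 | 79.2 v 81.8 | 78 v 82 |

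Runs A and B used 22 uneven sites and 180 patients. The Monte Carlo standard error of a power figure in run B is about 0.9 points. Stratified minus planned is −2.2, −2.2 and −1 at SD 0; about −1 to 0 at SD 0.4 to 0.5; +2.2, +1.7 and +3 at SD 0.8; and +3.5, +2.6 and +4 at SD 1.0. The stratified test's type I error was 3.9% to 4.6%.

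To judge these SDs, the latent intraclass correlation is SD²/(SD² + 3.29). SD 0.4 gives 0.16/3.45 = 0.05, SD 0.8 gives 0.64/3.93 = 0.16, and SD 1.0 gives 1/4.29 = 0.23.

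**The case against.** The strongest reply is that the planned test is valid and matches the sample size calculation, and that stratifying helps only if sites differ a good deal. At SD 0.4 to 0.5 there is nothing to gain, and at SD 0 a point or two is lost. The article gives no figure for site variation. All of this stands and limits the point to a refinement. Site differences are plausible, because Risk to participants leaves prescribing to the treating clinician and Study population describes a varied case mix, but plausibility is not a variance.

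Three stronger readings are tempting and should be resisted.

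- A reader might infer that leaving out site invalidates the primary test. It does not: type I error never exceeded 5% in the simulations.
- A reader might look at rank tests, where the contrast is larger (at SD 1.0, 74% power unstratified and 80% stratified). The plan does not use a rank test. Moving from the planned test to a stratified rank test would cost about 8 points if sites did not differ (80% to 72%). It would also turn a hypothesis about the frequency distribution into one about location.
- A reader might infer that centre terms will bias or break the secondary binary analyses. The article does not say that centre is a fixed effect, and including the stratification factor is sound practice. Even with fixed centres, the log odds ratio was exaggerated by only about 8% to 11% at assumed event rates of 30% to 40%. At an assumed 3% rate, 6% to 9% of fits gave no finite treatment estimate. The article gives no event rates, and sparse-data handling can be left to the analysis plan.

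**Conclusion.** The inconsistency is real and stated in the text: site governs the randomisation and enters the secondary models, but is absent from the primary test. Its consequence is small. The planned test controls type I error at about 3.5% to 5%. Relative to its own stratified version, it forgoes about 2 to 4 points of power under Model 3 if the between-site SD is 0.8 to 1.0. It gains about 1 to 2 points if sites do not differ. This is a forgone gain rather than a fall: the planned test's power stayed between 77% and 79% across intraclass correlations of 0 to 0.2. The sizes depend on assumed site variance, site sizes and block lengths, none of which the article gives. Nothing here counts against the secondary analyses.

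**What to change.** Replace the primary test with the Cochran-Mantel-Haenszel general association test of arm against the eight AFD categories, stratified by the site unit used in the randomisation system, on 7 df. State whether that unit is the Trust or the ICU. Keep the unstratified chi-squared test as a sensitivity analysis. Record the change before anyone sees outcomes by arm.

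The question stays the same, a difference in the AFD frequency distribution, and the sample size need not change. Sites whose patients are all in one arm or all in one AFD category simply add nothing to the statistic, so no pooling rule is needed. The cost is a sentence in the plan, a few lines of code and, if sites turn out not to differ, about 1 to 2 points of power.

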### Statistical analysis

Baseline clinical data will be compared between trial arms for balance using graphical and summary statistics appropriate for the data type of each variable. No formal tests of equality will be carried out. The primary outcome measure will be analysed by a chi-squared test on a 2 × 8 table of study arm versus AFD categories. Secondary outcome measures will be analysed by fitting appropriate generalised linear models with intervention and centre as covariates. Link functions will be determined by the type of outcome variable. A sub-group analysis for patients with trauma or head injury will be included as will a sub-group analysis based on clinician assessment of likelihood of VAP. Data analysis will be performed on an intention-to-treat basis, although other exploratory analyses including per-protocol analysis will be considered. A per-protocol analysis will be performed excluding patients who were randomised to the biomarker-guided recommendation on antibiotics arm, but who had a technical issue with the assay and therefore defaulted to standard care.

A within-trial cost analysis will be undertaken to assess the hospital resource use from the point of randomisation until hospital discharge or death, whichever occurs first, for a maximum of 56 days. Patient-level hospital resource use will be estimated from length of ICU stay and length of hospital stay. Multiple regression analyses will be performed to examine patient factors, which are potentially associated with costs. The robustness of the results will be evaluated using sensitivity analyses.

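### The exploratory per-protocol analysis drops assay failures from the biomarker arm only, so it is not a randomised comparison; a complier-average estimate would answer the same question

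*Protocol article*

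**What the plan says.** All of the rule stands in the Protocol article, Statistical analysis. The general statement is: "Data analysis will be performed on an intention-to-treat basis, although other exploratory analyses including per-protocol analysis will be considered". The sentence after it goes further and commits to a per-protocol analysis "excluding patients who were randomised to the biomarker-guided recommendation on antibiotics arm, but who had a technical issue with the assay". Such patients, it adds, were managed in the same way as controls. No exclusion is given for the control arm.

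Two other sections decide whether a matching control exclusion would be possible:

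- Randomisation and blinding: "the technician then initiates randomisation through the Newcastle Clinical Trials Unit", and the message for a control patient is "routine use of antibiotics: do not analyse sample on arrival". An assay can therefore fail only after allocation, and only in the biomarker arm.
- Data collection: the biological data listed are "concentrations of IL-1β and IL-8 in the BAL fluid for patients who are randomised to the intervention arm". No biomarker measurement is listed for controls.

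**The concern.** Technical failure of the assay is seen only where the assay is run. Control patients whose samples would also have failed cannot be identified and stay in the comparison. The per-protocol contrast is assay successes against all controls.

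This matters if failures are not a random sample of patients. The section on the assay and laboratory set-up describes six hubs, ICUs up to an expected 1.5 hours away, samples sent on ice, and technicians who may have little flow cytometry experience. Failures could cluster by hub, and so by site. Randomisation is stratified by site, and removing failures from one arm disturbs that balance. If antibiotic practice differs between sites, a difference in AFD could appear or disappear even when failure has nothing to do with the individual patient's prognosis.

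The likely use of this analysis is to show what the test does when it works, which is a reasonable question. The stated rule answers it with a comparison that randomisation does not protect.

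**Working it through.** **Inputs from the Protocol article.** Table 1, standard care: 55, 10, 10, 5, 5, 5, 5, 5% for 0 to 7 AFD. Model 3: 30, 20, 15, 10, 10, 5, 5, 5%. Total sample size 210, so 105 per arm. No assay failure rate is given, and nothing on AFD in patients whose assay fails. Those two quantities are assumptions below.

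**Step 1: reproduce the plan's figure.** Effect size = ½ Σ (p − m)²/(p + m). For Model 3:

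½ × (0.0625/0.85 + 0.01/0.30 + 0.0025/0.25 + 0.0025/0.15 + 0.0025/0.15) = 0.0751.

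The plan prints 0.075. With 7 degrees of freedom, and alpha 0.05 and 80% power assumed because they are not stated, this needs 96 per arm, as printed. The baseline distribution is thus read as the plan reads it. Mean AFD is 1.55 under standard care and 2.10 under Model 3, a shift of 0.55 days. The share with 0 AFD falls by 25 points.

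**Step 2: what the exclusion does when the test has no effect.** Let q be the share of biomarker-arm assays that fail and z the share of those patients with 0 AFD. After exclusion the biomarker arm's share with 0 AFD is (0.55 − qz)/(1 − q). The control share stays at 0.55.

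| q | z | Biomarker arm after exclusion | Shift from 55% |
|---|---|---|---|
| 0.10 | 0.80 | (0.55 − 0.08)/0.90 = 0.522 | −2.8 points |
| 0.10 | 0.55 | (0.55 − 0.055)/0.90 = 0.550 | 0 |
| 0.10 | 0.40 | (0.55 − 0.04)/0.90 = 0.567 | +1.7 points |

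A negative shift flatters the biomarker arm and a positive one counts against it.

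**Step 3: the same on mean AFD.** The spurious difference is q × d, where d is the mean AFD of assay successes minus that of failures. For d = 1 day it is 0.02, 0.05, 0.10 and 0.15 days at q = 2%, 5%, 10% and 15%. It changes sign with d.

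**Step 4: an upper bound in one direction.** If every failure had 0 AFD, the mean difference with no true effect would be 0.03, 0.08, 0.17 and 0.27 days at the same four failure rates. With 105 per arm before exclusion, the 2 × 8 chi-squared test at a nominal 5% would reject in 5.1%, 5.4%, 6.9% and 10.0% of trials.

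**Step 5: the complier-average estimate in the same scenarios.** With no effect, the intention-to-treat difference is 55 − 55 = 0, and 0/0.90 = 0 whatever z is. Now suppose that the working test lowers the share with 0 AFD by 25 points among assay successes and failures receive standard care. The intention-to-treat difference is 0.90 × 25 = 22.5 points, and 22.5/0.90 = 25. The per-protocol difference is 55 − (52.2 − 25) = 27.8 points if z = 0.80, and 55 − (56.7 − 25) = 23.3 points if z = 0.40.

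**Step 6: loss of precision.** At q = 0.10 the intention-to-treat interval is scaled by 1/0.90 = 1.11. The per-protocol comparison has 94.5 against 105 patients, which scales it by √[(1/94.5 + 1/105)/(2/105)] = 1.03. The complier interval is therefore about 1.11/1.03 = 1.08 times as wide as the per-protocol one, taking equal variances and a known q.

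**The case against.** The strongest reply is that little depends on this analysis. Intention to treat is the stated basis, per-protocol is called exploratory, and neither the sample size nor the primary test uses the reduced set. That stands, and it limits the weight of the point.

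It can also be said that the exclusion is for a technical fault, not for clinician non-adherence or clinical course. Standard procedures, central training, weekly quality control and a travel limit may make failures close to random within site, and then the bias is negligible. This too is fair: nothing in the article links failure to prognosis or antibiotic use. But the design cannot demonstrate it, because failure is never observed in controls.

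Three stronger readings should be resisted:

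- A reader might infer that the primary result is compromised. It is not; failed-assay patients stay in their randomised arm there.
- A reader might infer that the exclusion favours the biomarker test, or favours it by a large amount. That needs the assumption that failures have fewer AFD than other patients, and for a large shift also that failures are common. The article supports neither.
- A reader might infer that the complier estimate needs no assumptions because of the design. Controls receiving no result rests on an instruction emailed to the technician. That a failed assay leaves prescribing unchanged is supported by the default to standard care, and by control teams also being told the allocation, but not guaranteed.

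**Conclusion.** The point holds for the exploratory per-protocol analysis only. As written, that analysis conditions on a post-randomisation event in one arm with no counterpart in the other, so randomisation does not protect it. The bias is unknown in size and direction: zero if failures are unrelated to site and prognosis, and roughly −3 to +2 points on the share with 0 AFD in the 10% illustration, against the 25 points of Model 3. Those figures rest on an assumed failure rate and assumed outcomes in failures; the article gives neither. The change is worth making because a method that keeps every randomised patient answers the same question at almost no cost.

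**What to change.** - **Estimate.** For the effect of a working test, prespecify a complier-average causal effect: the intention-to-treat difference divided by the proportion of the biomarker arm for whom a result was issued, adjusted for site, with a bootstrap or two-stage least squares confidence interval. Apply it to AFD as a continuous outcome, which is already a secondary outcome, or to the share with 0 AFD. The ratio does not carry over to the 2 × 8 chi-squared test.
- **Assumptions.** State that controls receive no result and that a failed assay does not itself change prescribing.
- **If the per-protocol comparison is kept.** Label it non-randomised and supportive, and report the site, baseline data and AFD of the failed-assay patients.
- **Wording.** Reconcile the two consecutive sentences, one of which only considers a per-protocol analysis while the next commits to it.

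Assaying stored control samples later is not a substitute. The article does not document that they are kept, and failures from transport or an instrument fault on the day would not recur in a later batch.

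The cost is one extra analysis and a somewhat wider interval (about 8% wider than per-protocol at 10% failures). No new data are needed, and the sample size and primary analysis do not change.

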**Methods/Design:**

This is a prospective, multi-centre, randomised, controlled trial to determine whether a rapid biomarker-based exclusion of VAP results in fewer antibiotics and improved antimicrobial management. Patients with clinically suspected VAP undergo BAL, and VAP is confirmed by growth of a potential pathogen at > 10^4^ colony-forming units per millilitre (CFU/ml). Patients are randomised 1:1, to either a ‘biomarker-guided recommendation on antibiotics’ in which BAL fluid is tested for IL-1β and IL-8 in addition to routine microbiology testing, or to ‘routine use of antibiotics’ in which BAL undergoes routine microbiology testing only. Clinical teams are blinded to intervention until 6 hours after randomisation, when biomarker results are reported to the clinician. The primary outcome is a change in the frequency distribution of antibiotic-free days (AFD) in the 7 days following BAL. Secondary outcome measures include antibiotic use at 14 and 28 days; ventilator-free days; 28-day mortality and ICU mortality; sequential organ failure assessment (SOFA) at days 3, 7 and 14; duration of stay in critical care and the hospital; antibiotic-associated infections; and antibiotic-resistant pathogen cultures up to hospital discharge, death or 56 days. A healthcare-resource-utilisation analysis will be calculated from the duration of critical care and hospital stay. In addition, safety data will be collected with respect to performing BAL. A sample size of 210 will be required to detect a clinically significant shift in the distribution of AFD towards more patients having fewer antibiotics and therefore more AFD.

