### Biomarker assay and laboratory set up

The biomarker assay is performed in six NHS or university laboratories that act as testing ‘hubs’. Participating ICUs had to be within an expected travel time of 1.5 hours of a hub. BAL fluid samples are transported to the laboratory on ice immediately after sampling and measurement of BAL fluid IL-1β and IL-8 by cytometric bead array is performed with minimal delay on arrival. IL-1β and IL-8 are combined by logistic regression by the equation, established in the validation study [5]:$$ -2.7385 + 1.4633 \times \log 10\left(1 + \mathrm{I}\mathrm{L}-1\upbeta \right)-0.2721 \times \log 10\left(1 + \mathrm{I}\mathrm{L}-8\right) $$

VAP is excluded if the regression output falls below a defined level (-1.7616).

All equipment, reagents and ongoing maintenance are supplied by the study’s industry partner, Becton Dickinson Biosciences (Franklin Lakes, NJ, USA). Each hub has been issued an Accuri C6 flow cytometer. This is a benchtop flow cytometer designed for its ease of use. The biomarker assay and all Accuri standard operating procedures (SOPs) have been designed such that they can be carried out by healthcare service laboratory technicians with limited flow cytometry experience. Centralised training in the biomarker assay and Accuri C6 was provided by investigators and scientists from Newcastle University and Becton Dickinson.

Accuri quality control tests are performed once a week by each hub, and these data are monitored by the flow cytometry core facility in Newcastle University. Technical support is provided by the investigators at Newcastle University and by Becton Dickinson.

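### The within-trial cost analysis counts only durations of stay, so it supports a statement on bed-days but not on the cost of the biomarker strategy

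*Protocol article*

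**What the plan says.** The cost paragraph under Statistical analysis opens: "A within-trial cost analysis will be undertaken to assess the hospital resource use from the point of randomisation until hospital discharge or death", with a ceiling of 56 days. The next sentence names the inputs: "Patient-level hospital resource use will be estimated from length of ICU stay and length of hospital stay". It then adds a regression ("Multiple regression analyses will be performed to examine patient factors, which are potentially associated with costs") and an unspecified check ("The robustness of the results will be evaluated using sensitivity analyses").

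The same analysis appears in two other places. The Abstract has: "A healthcare-resource-utilisation analysis will be calculated from the duration of critical care and hospital stay". The Secondary outcome measures section has: "A healthcare-resource-utilisation analysis will be calculated from the duration of level 2 care, level 3 care and hospital stay", again up to discharge, death or 56 days.

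The cost paragraph does not itself name a comparison between arms. One follows from the general rule for secondary outcomes: "Secondary outcome measures will be analysed by fitting appropriate generalised linear models with intervention and centre as covariates".

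On the assay, Biomarker assay and laboratory set up says: "All equipment, reagents and ongoing maintenance are supplied by" the study's industry partner. Antibiotic days at 7, 14 and 28 days are listed as a secondary outcome, but no sentence links them to the cost analysis.

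**The concern.** A cost comparison between two strategies should include the resources in which they differ. Here the arms are separated by a flow-cytometric assay taking about 6 hours, with technician work at a hub laboratory. The expected benefit is fewer days of antibiotics. Neither item is among the stated inputs. Because the industry partner supplies the reagents and equipment, hospital records are unlikely to pick up that cost by another route.

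If mean stay were the same in both arms, the analysis would report no difference, whatever the test cost and whatever was saved on antibiotics. A reader could take that as evidence that the strategy is cost-neutral, and the analysis could not bear that conclusion.

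The inconsistent bed-day inputs add a smaller problem. Secondary outcome measures separates high dependency (level 2) from intensive care (level 3). Statistical analysis has only ICU and total hospital stay. Two analysts following different sections could assign different costs to the same patient.

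**Working it through.** The article states no cost figure, so there is nothing to reproduce. The check has two parts: what the three statements of the analysis count, and what the omitted items do to a between-arm difference.

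**Inputs counted, side by side**

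| Place | Bed-day inputs | Assay | Antibiotics |
|---|---|---|---|
| Abstract, Methods/Design | critical care, hospital | not listed | not listed |
| Secondary outcome measures | level 2, level 3, hospital | not listed | not listed |
| Statistical analysis | ICU, hospital | not listed | not listed |

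Under the third row, level 2 days spent outside an ICU cannot be told apart from ward days. Under the second row they can.

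**Direction of the error**

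Let D be the between-arm difference (intervention minus control) in bed-day cost, T the cost of one biomarker test, A the cost of one antibiotic day, and g the mean number of antibiotic days avoided per patient.

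- Difference including both items: D + T - A × g
- Difference under the stated rule: D
- Net omitted cost per intervention patient: T - A × g

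If this quantity is positive, the stated rule makes the test arm look cheaper than it is. If it is negative, the rule makes it look dearer.

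For g, take the gain in mean antibiotic-free days (AFD) over 7 days from Table 1, treating each day gained as one antibiotic day avoided:

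- Standard care: 0.10×1 + 0.10×2 + 0.05×(3+4+5+6+7) = 1.55
- Model 3: 0.20×1 + 0.15×2 + 0.10×3 + 0.10×4 + 0.05×(5+6+7) = 2.10
- g = 2.10 - 1.55 = 0.55 days

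The other models follow in the same way. The break-even ratio A/T is 1/g:

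| Model | Mean AFD | g | Break-even A/T |
|---|---|---|---|
| 1 | 1.75 | 0.20 | 5.00 |
| 2 | 1.90 | 0.35 | 2.86 |
| 3 | 2.10 | 0.55 | 1.82 |
| 4 | 2.20 | 0.65 | 1.54 |

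The article gives neither T nor A. The values below are assumptions, in arbitrary currency units, chosen only to see whether the sign is stable. They show T - 0.55A under Model 3:

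| T | A = 5 | A = 50 | A = 100 | A = 200 | A = 400 |
|---|---|---|---|---|---|
| 20 | +17.25 | -7.5 | -35 | -90 | -200 |
| 50 | +47.25 | +22.5 | -5 | -60 | -170 |
| 100 | +97.25 | +72.5 | +45 | -10 | -120 |
| 200 | +197.25 | +172.5 | +145 | +90 | -20 |

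The sign changes in every row. The document therefore fixes neither the size nor the direction of the net error.

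**The case against.** The strongest reply is about scope. The paragraph sets out to assess hospital resource use, and the other two places call it a resource-utilisation analysis. Bed-days are a coherent, if narrow, measure of that. The article promises no cost-effectiveness analysis and does not ask whether the strategy is worth its price. This stands, and it is why relabelling the analysis is an acceptable remedy. It does not remove the point, because the paragraph also calls itself a cost analysis and plans regressions on costs.

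A second reply is that this is a condensed article, and that unit costs and the content of the sensitivity analyses normally sit in a fuller document. That holds for prices. It is weaker for the list of resources, which is stated three times and is confined to stay each time. Still, it would go too far to say that the test cost can never enter; the article shows only that the stated inputs do not include it.

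Two stronger readings are tempting. A reader might infer that the comparison is biased in favour of the test. Only the missing assay cost acts that way. The missing antibiotic saving acts against the test if the test works, and the net sign depends on prices not given. A reader might also count sample transport as a cost of the intervention arm alone. The article does not support this. The transport description is not limited to one arm, and under Randomisation and blinding the control-arm instruction concerns what the technician does with a sample when it arrives, which implies that control samples travel too.

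Finally, a between-arm model is already implied by the rule for secondary outcomes. That is correct, so the arm comparison needs only to be made explicit.

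**Conclusion.** The point holds in a limited form. As stated in all three places, the analysis is built from durations of stay. It leaves out the assay and antibiotics, and its bed-day inputs differ between Secondary outcome measures and Statistical analysis. It can support a statement on bed-day use but not on the cost of the biomarker strategy.

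Under Model 3 the net omitted cost is T - 0.55A per intervention patient. It favours the test if A is below 1.82 × T and works against it if A is above. This rests on Table 1's illustrative distributions, on a 7-day window, and on equating a gained antibiotic-free day with a saved antibiotic day. No monetary size can be given from the document. With no bed-day price either, it cannot be shown how large the omission is relative to total cost.

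This is an inexpensive improvement to a secondary analysis. The primary outcome and sample size are not touched.

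**What to change.** In the cost paragraph under Statistical analysis:

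1. Use the bed-day inputs of Secondary outcome measures throughout: level 3 days, level 2 days and other hospital days, each at its unit cost.
2. Add a fixed cost per biomarker test in the intervention arm, covering reagents at list price (although the partner supplies them in the trial) and technician time.
3. Add antibiotic days at unit cost over the 28 days for which they are recorded, and say that this window is shorter than the 56 days used for stay.
4. State that the between-arm difference in mean cost will be reported with its interval, in addition to the regression on patient factors.
5. Vary the test price in the sensitivity analyses already planned.

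If the unit costs cannot be obtained, name the analysis bed-day resource use in all three places, still align the level 2 wording, and draw no conclusion on cost.

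The first option needs a few unit costs and no patient data beyond the outcomes already listed. Its downside is that the cost figure may turn out less favourable to the test. The second option costs only a change of wording, but leaves the cost of the strategy unanswered.
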